### 9.4.3 Analysis of the Secondary Endpoint(s)

Our primary secondary outcome is to select the PBPK model that best characterizes the data using individual and population acceptance criteria. To apply the acceptance criteria, we will simulate plasma drug concentrations for everyone using the PBPK model and will compare predictions with observed concentrations. We will assess model bias by calculating the average fold error between predicted and observed concentrations: AFE=10[1/N∑log(predicted/observed)]. The AFE indicates model under- (AFE<1) or over-prediction (AFE>1) when compared with observed values of the individual. We will assess model precision by calculating the absolute average fold error: AAFE= 10[1/N∑|log(predicted/observed) |] for each curve. We will consider <30% bias (AFE 0.7–1.3) and ≤2-AAFE reasonable predictions. We will assess population predictability by generating a prediction interval (5th to 95th percentile) of drug concentrations per time point for the population and quantifying the number of observed concentrations that fall outside of the prediction interval. The model will be accepted if 90% of observed concentrations fall within the prediction interval.

Differences in exploratory outcomes will be analyzed by unpaired t-tests (for ratio measures such as blood loss) or by Mann-Whiney tests (for ordinal measures such as parental anxiety scale). However, the pilot study is not designed to determine a difference in these outcomes but to determine the feasibility and procedures of the main trial.

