**Figure 3: Study Protocol Flow**

## 4.2 Scientific Rationale for Study Design

In 2018, a case report documented that a single dose of nebulized tranexamic acid (TXA) prevented operative management in a three-year-old with PTH^10^. A subsequent randomized controlled trial in adults documented a decrease in blood loss and secondary hemorrhage using nebulized TXA for hemoptysis^20^. The current use of antifibrinolytics (e.g., TXA or e-aminocaproic acid) is rarely used to treat PTH. Therefore, there is an essential need to test the efficacy of nebulized TXA to decrease the severity of PTH. Our retrospective cohort study documented that nebulized TXA may be effective in decreasing the need for operative intervention^13^. However, retrospective studies have significant bias indicating the need for a multi-center, randomized, double-blinded, controlled clinical trial. As we do not have an established alternative drug the standard is to test the drug vs. a placebo such as nebulized normal saline. The power analysis and 1:1 study design reduces bias and confounders for the evaluation of study outcomes. Even if the patient presents without active bleeding, it is possible that nebulized TXA has the potential to stabilize the clot to prevent future bleeding.

A verified pulmonary PBPK model can set the dose of the phase 3 trial. A pulmonary PBPK model incorporates all known intravenous, oral, or local TXA administration PK and pulmonary physiology data. This model only needs verification by small number of systematic samples, compared to traditional pharmacokinetic studies that require multiple samples using different doses and ages of patient. A verified model can then be use predict the drug for the phase 3 trial with the lowest systematic absorption, which will minimize side effects.

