## 4.3 Justification for Dose

We conducted a study evaluating nebulized TXA in 58 children with PTH^13^. Three consecutive doses of nebulized TXA were given to each child, 500 mg per dose for children >25 kg and 250 mg per dose for children <25 kg. These doses were picked from the earlier literature ^9,21^ that documented success in reducing hemoptysis. Our single-arm study demonstrated that nebulized TXA significantly decreased the need for surgical management of PTH by 44% compared to historical controls. There was no associated increase in adverse events or delays in care to patients who required a surgical intervention. This study found that some children responded after one dose, but most children responded after two doses. For the pilot trial, we propose to administer three doses of 500 mg (total 1500 mg) of nebulized TXA to each child enrolled regardless of their weight. This was further confirmed by a retrospective study that delivered 500 mg/dL to several children less than 7 years of age(3). We considered dose choice based on the need to balance the amount of TXA with a goal to decrease the severity of PTH. Using TXA improves our safety because it is an approved medication that has a minimal and known side effect profile.

We chose a total dose of 1500 mg because it does not exceed the maximum intravenous dose approved for the average weight of a four-year-old. Neurological and cardiac surgical procedures have used over 100 mg/kg intravenous loading dose of TXA and then 10 mg/kg/hour drip with minimal side effect^22,23^. We hope that nebulization to deliver TXA will result in a lower systematic peak of TXA and yet because it is focused on the source of the bleed it remains effective. Several studies have documented that peak TXA concentration is much reduced with topical versus intravenous administration^2425^. Lastly, the potential benefits of a higher dose of TXA is significantly less risk than risk of neurocognitive injuries documented by repeat exposures to anesthesia and surgery. In summary, the investigators chose a fixed dose based on the two points: 1) Nebulized TXA is expected to have very little systemic uptake, and we wish to maximize safe effect, and 2) Prior surgical studies have not shown an increased risk of AEs with intravenous TXA compared to placebo.

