# 5 Study Population

## 5.1 Inclusion Criteria

1. Received a tonsillectomy

2. Presents to the ED with secondary* post-tonsillectomy hemorrhage

3. Children between age of 2 to 17 years of age (i.e., before their 18^th^ birthday)

*Secondary post-tonsillectomy hemorrhage is defined as greater than 24 hours from their primary tonsillectomy operation (arrival in recovery/PACU).

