**Pharmacokinetic and Pharmacodynamic Testing:** Pharmacokinetics samples will be collected after completion of the last nebulized treatment received within sixty minutes. A second time point should then be collected after sixty minutes up to eight hours from last nebulization, separated from the previous time point by at least sixty to ninety minutes. The results from the TXA level measurements will be used for research purposes only and not be available to clinicians. The serum TXA levels will be used to develop a TXA PK model and determine the population variability. We will develop a base model to determine a best-fit compartmental model, distribution, and elimination kinetics. We will also use stochastic models to evaluate between-subject variability in PK parameters. Serum TXA concentrations will use 200 microliters of plasma measured by an ultra-high performance liquid chromatography tandem mass spectrometry method specifically developed for sensitive and precise analysis of low TXA concentrations at the U.S. Army Institute for Surgical Research. Moreover, we will use the remaining 200 microliters to measure pharmacodynamics effects of nebulized TXA in the plasma. ELISA can use minimal plasma volume (<300 μL) to run commercial kits measuring Plasmin-antiplasmin (PAP) complexes, D-dimer, Thrombin-antithrombin (TAT) complexes, Prothrombin fragment F1+2 (F1+2), and Plasminogen activator inhibitor-1 (PAI-1). Combination of pharmacokinetic and pharmacodynamic effects achieves the primary goal to determine drug systematic compared to local effects.

The protocol will adhere to the following guidelines when scheduling procedures to collect pharmacokinetic samples:

- Samples will be collected in EDTA 1 mL tubes (Fisher Scientific Catalog number 22-030-402). Within 2 hours of sample collection, tube will spin in a calibrated centrifuge. Please see attached centrifuge calibration standard of operating procedure.
- Centrifuge procedures consist of:
  - Place sample in centrifuge with appropriate weighted balance
  - Centrifuge sample at 2500 RPM for ten minutes at room temperature
  - Remove sample from centrifuge, using a pipette remove plasma above buffy coat and place into a clean Eppendorf tube (roughly 0.4-0.6 mL).
  - Place Eppendorf tube back in centrifuge with appropriate balance.
  - Centrifuge second time at 2500 RPM for ten minutes at room temperature.

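### The single population prediction interval in protocol 9.4.3 has little power to detect age- or size-specific error in the PBPK model

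*Protocol*

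**What the plan says.** Section 9.4.3 sets out to "select the PBPK model that best characterizes the data using individual and population acceptance criteria". It has three numerical checks.

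- Fold error: "We will consider <30% bias (AFE 0.7–1.3) and ≤2-AAFE reasonable predictions". AFE measures bias and AAFE measures precision.
- Coverage: an interval obtained by "generating a prediction interval (5th to 95th percentile) of drug concentrations per time point for the population".
- Decision: "The model will be accepted if 90% of observed concentrations fall within the prediction interval". This is the only sentence in the section that ties a criterion to acceptance.

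The interval is indexed by time point, and no age or weight strata are mentioned. Three other passages bear on it. Section 5.1 enrols "Children between age of 2 to 17 years of age". In 4.3 the sponsor writes "we propose to administer three doses of 500 mg (total 1500 mg) of nebulized TXA to each child enrolled regardless of their weight". Section 4.2 gives the purpose: "A verified pulmonary PBPK model can set the dose of the phase 3 trial". Sampling in 8.2.2 is timed from the last dose the child actually received: "Pharmacokinetics samples will be collected after completion of the last nebulized treatment received within sixty minutes".

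**The concern.** If the model is to inform a dose for children from toddlers to adolescents, the verification has to show that it predicts the right level for a child of a given size. An interval pooled over the whole age range asks only whether an observed value is plausible for some child in the population. It is wider than the interval for a child of known size.

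The interval also comes from the model under test. A model that exaggerates the contrast between small and large children widens its own interval and gains coverage. The rule has no upper limit on coverage and no check by age. A correct model has expected coverage of exactly 90%, so it sits on the threshold. A model with a material error in one age group could therefore be declared verified.

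**Working it through.** **Inputs from the protocol.** 5th–95th percentile interval; 90% threshold; AFE 0.7–1.3; AAFE ≤2 (9.4.3). Two samples per participant (section 3). 1:1 allocation (4.1). Single site: 6 TXA children (5.5), so 12 TXA concentrations. Multi-site: 0.6 × 3 × 12 = 21.6, rounded up to 22 (9.2), so about 11 TXA children and 22 concentrations.

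**Assumptions, because the protocol gives no values.** Ages uniform from 2 up to the 18th birthday; median weight from about 12 to 65 kg; concentration proportional to weight^-k with k = 0.75 or 1; between-child CV 30% or 50%; residual CV 10%; log-normal errors.

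**Step 1: a correct model.** Nominal coverage is 0.95 − 0.05 = 0.90, equal to the threshold. If observations were independent, acceptance would be:

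- 12 values, at least 11 inside: 0.9^12 + 12 × 0.1 × 0.9^11 = 0.282 + 0.377 = 0.659.
- 22 values, at least 20 inside: 0.620.

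**Step 2: interval width.** For a child of known size the upper/lower ratio is exp(2 × 1.645 × √(ln(1 + CV²) + ln(1.01))). At CV 30% this is exp(3.29 × 0.310) = 2.8, and at CV 50% it is exp(3.29 × 0.483) = 4.9. The pooled interval of a correct model has a ratio of about 5 to 10.

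**Step 3: why an outward error helps.** If the model is two-fold too high in the youngest, or two-fold too low in the oldest, the pooled interval widens and true coverage rises to about 0.95. With independent values, acceptance becomes:

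- 12 values: 0.95^12 + 12 × 0.05 × 0.95^11 = 0.540 + 0.341 = 0.882.
- 22 values: 0.324 + 0.375 + 0.207 = 0.905.

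Two correlated samples per child lower these somewhat, as step 4 shows.

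**Step 4: simulation.** 20,000 trials per setting. The pooled interval is the 5th–95th percentile of the model's own simulated population. The matched interval is the child's predicted log value ± 1.645 total SD. AFE and AAFE are computed across children. Acceptance with 11 TXA children, ranges over CV and k:

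| Model | Coverage, pooled | Coverage, matched | All three criteria, pooled | All three, matched |
|---|---|---|---|---|
| Correct | 62–64% | 62–64% | 62–63% | 62–63% |
| Two-fold high, under 6 | 85–87% | 13–32% | 62–68% | 13–29% |
| Two-fold low, 12 and over | 86–87% | 5–21% | 61–67% | 4–20% |
| Both errors | over 99% | 0.3–8% | 67–86% | 0.3–8% |

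With 6 TXA children and the pooled interval, either single-group error passes coverage 76–79% of the time, against 58–62% for a correct model. With all three criteria it is 50–58% against 54–61%. Matched intervals with all three criteria bring the single-group errors to 11–31%.

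**Step 5: direction and robustness.** Inward errors, two-fold low in the youngest or two-fold high in the oldest, narrow the interval. With 6 TXA children they pass coverage only 14–38% of the time. For outward errors under the coverage rule, the ordering in the table held at CV 80% (79–86% against 61–66%), with within-child correlation from 0 to 0.9, and with a younger age mix.

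**The case against.** The strongest reply is that coverage is only the population half of 9.4.3. The section names individual criteria, simulates every participant, and refers AFE to the individual's observed values; 9.1 also frames the modelling aim in fold-error terms. A reader might infer that the plan has no check on the right level for the right child. The text does not support that. Read child by child, AFE is informative: at CV 30–50%, 83–92% of under-6 children fall outside 0.7–1.3 when the model is two-fold high there, against 31–52% under a correct model.

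A reader might also infer that the plan as a whole favours a wrong model. That is not supported either. Once AFE and AAFE are required across children, the advantage of a single-group error mostly disappears. The exception is some settings with a younger age mix, where under-prediction in the oldest still leads (85–86% against 61–62% at CV 30% with 11 TXA children).

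Three further limits stand. The several-fold spread by body size is an assumption, since the protocol treats absorption as unknown. The fixed dose is not the only cause: with no weight gradient and 6 TXA children, the wrong models still pass coverage at 68–79% against 62–67%. Added spread from children who receive fewer doses is plausible but was not simulated.

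The reply does not dispose of the point. Section 9.4.3 attaches acceptance to coverage alone, gives no joint rule, and does not say how many individual failures would sink the model. Requiring AFE 0.7–1.3 of every child is not workable: a correct model meets it in only 48–69% of children, and even 0.69^11 = 0.017, so it would be rejected more than 98% of the time. No check by age is specified.

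**Conclusion.** The point holds in a limited form. As worded, the acceptance rule in 9.4.3 has little power against age- or size-specific error. On coverage alone it accepts a model that is two-fold wrong outward in one age group more often than a correct one: about 85–87% against 62–64% with 11 TXA children, and 76–79% against 58–62% with 6. With the fold-error limits added, such a model passes about as often as a correct one (50–68% against 54–63%). Child-matched intervals with the same limits would bring that to about 4–31%.

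The sizes rest on the assumed CVs, weights, exponents and age mix, and on reading the interval as a single one for ages 2 to 17. The claim concerns outward errors only. It does not show that the model will be wrong, and it is no comment on the dose. The pilot can run as designed, but a model accepted under this rule would be weak support for the use described in 4.2.

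**What to change.** In 9.4.3:

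1. For each observed concentration, simulate the 5th–95th percentile interval in virtual children with that child's age, weight, nebulizations received and actual sampling time. Score the observation against its own interval.
2. State that the model is accepted only if coverage, AFE and AAFE are all met, and how AFE and AAFE are combined across children. Align the fold-error limits with those in 9.1.
3. Report misses and AFE by age group (for example under 6, 6–11, 12 and over) descriptively. With uniform ages a quarter of children are under 6: about 1.5 of 6 or 2.75 of 11 TXA children. With 6, the chance of one or none is 0.75^6 + 6 × 0.25 × 0.75^5 = 0.53, so a formal test by group would mean little.

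The cost is wording and more simulation runs. No new data are needed: weight, nebulizations given and sample collection times are already planned. There would no longer be a single band to plot. The change does not alter the threshold itself: a correct model would still fail 90% coverage about 36–40% of the time, and the sponsor should know that when setting the rule.

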# 9 Statistical Considerations

## 9.1 Statistical Hypotheses

The pilot study is not designed to test an efficacy hypothesis, but rather to determine the feasibility for patient enrollment and the number of doses received per patient.

**Our primary hypothesis** for the single site and the multi-site study is that we can enroll at least 0.6 patients per site per month and deliver a minimum of two out of three planned nebulized TXA doses to >90% of enrolled patients.  The single site study will only be one year and the multi-site study for 18 months. We will test each of this (yes/no) hypothesis using a Mantel Haenszel test stratified by site for a total of 12 patients for the single-site study for greater than 24 nebulization and for the multi-site study up to 22 patients with greater than 44 nebulization's recorded as delivered.

**Our secondary goals** will be to determine if nebulized TXA prevents going to the OR for PTH and utilization of blood products. These goals are not powered to be tested in the pilot study. **Our second aim** is to verify a pulmonary physiological based pharmacokinetic (PBPK) model (i.e., nasal cavity, pharynx, and lungs) will predict the change in the area under the curve (AUC0-α) of TXA concentration in systemic compartments with accuracy (average absolute fold error <2) and precision (average fold error <2). We will calculate the AUC of accuracy and precision of the model using the linear trapezoid rule. For the PBPK model, we will use previously published PK data to construct the model before verifying it with systematic samples.

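### Sections 9.1 and 9.4.3 set incompatible acceptance rules for the PBPK model, and the 90% coverage rule makes no allowance for sampling error

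*Protocol*

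**What the plan says.** Protocol 9.1 (Statistical Hypotheses) sets the second aim as verifying a pulmonary PBPK model that "will predict the change in the area under the curve" of TXA in systemic compartments, with "accuracy (average absolute fold error <2) and precision (average fold error <2"). It gives no lower limit for the average fold error (AFE). AUC is to be calculated by the linear trapezoid rule.

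Protocol 9.4.3 (Analysis of the Secondary Endpoint(s)) compares predicted with observed concentrations. It defines AFE and the absolute average fold error (AAFE) by formula and explains the direction of AFE: "The AFE indicates model under- (AFE<1) or over-prediction (AFE>1) when compared with observed values of the individual". It attaches the word precision to the other metric: "We will assess model precision by calculating the absolute average fold error". Its limits are: "We will consider <30% bias (AFE 0.7–1.3) and ≤2-AAFE reasonable predictions".

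Section 9.4.3 then adds a population check by "generating a prediction interval (5th to 95th percentile) of drug concentrations per time point for the population", with the decision rule "The model will be accepted if 90% of observed concentrations fall within the prediction interval".

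**The concern.** There are two separate problems.

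First, the two sections differ in three ways that matter: the AFE limit (one-sided below 2 against 0.7 to 1.3), the label precision (AFE in 9.1, AAFE in 9.4.3) and the quantity judged (AUC against concentrations). A small fourth difference is AAFE strictly below 2 against at most 2. With no statement of precedence, the same data could be reported as verifying the model under one section and not under the other.

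Second, the coverage rule sets its threshold at the value that a correct model attains on average. Chance alone will often put a correct model below it in a sample this small.

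The decision has consequences. Section 4.2 says a verified model can set the phase 3 dose, and the synopsis and section 3 list TXA concentrations among the primary objectives.

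**Working it through.** **Inputs.** Two blood samples per participant (section 3). Single-site study: 12 children, 6 on TXA (section 5.5). Multi-site study: 0.6 × 3 × 12 = 21.6, rounded up to 22 (section 9.2; the figure reproduces), so 11 on TXA at 1:1 allocation (section 4.1). Synopsis maximum: 30 children, so 15 on TXA. Saline recipients are expected to have no TXA, and log(predicted/observed) is then undefined, so only the TXA arm informs the check: 6 × 2 = 12, 11 × 2 = 22 or 15 × 2 = 30 concentrations. The protocol gives no pass or fail probability for any of these rules.

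**Fold-error limits.** Let d = log10(predicted/observed). Then AFE = 10^mean(d) and AAFE = 10^mean|d|. Because mean|d| ≥ |mean(d)|, AAFE ≥ max(AFE, 1/AFE). So AAFE < 2 already forces AFE to lie between 0.50 and 2.00, and the separate AFE < 2 limit in 9.1 adds nothing.

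For a constant ratio k, AFE = k and AAFE = max(k, 1/k), whether computed per child or pooled. The trapezoid rule is linear in concentration, so over the same sampling times the AUC ratio is also k.

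| k | AFE | AAFE | 9.1 | 9.4.3 |
|---|---|---|---|---|
| 0.50 | 0.50 | 2.00 | fail | fail |
| 0.51 | 0.51 | 1.96 | pass | fail |
| 0.69 | 0.69 | 1.45 | pass | fail |
| 0.70 | 0.70 | 1.43 | pass | pass |
| 1.30 | 1.30 | 1.30 | pass | pass |
| 1.50 | 1.50 | 1.50 | pass | fail |
| 1.99 | 1.99 | 1.99 | pass | fail |
| 2.00 | 2.00 | 2.00 | fail | fail |

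Every k with 0.50 < k < 0.70 or 1.30 < k < 2.00 passes 9.1 and fails 9.4.3.

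**Coverage rule.** Nominal coverage is 0.95 − 0.05 = 0.90. For a correct model and independent values, the number inside is X ~ Binomial(n, 0.90), and the rule needs X ≥ 0.9n, rounded up.

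- n = 12, at least 11 needed: P(accept) = 12 × 0.9^11 × 0.1 + 0.9^12 = 0.377 + 0.282 = 0.659, so rejection is 34.1%.
- n = 22, at least 20 needed: P(accept) = 0.281 + 0.241 + 0.098 = 0.620, so rejection is 38.0%.
- n = 30, at least 27 needed: P(accept) = 0.647, so rejection is 35.3%.

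A simulation with two Gaussian values per child and within-child correlation from 0 to 0.95 (400,000 runs per setting) gave rejection of 34–39% (n = 12), 37–38% (n = 22) and 35–38% (n = 30).

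Missing samples move the figure erratically because of rounding: 26% at n = 10, 32% at n = 20, 58% at n = 19. If the count were rounded down, rejection would be 11% (10 of 12) and 17% (19 of 22). Those are 83% and 86% inside, which does not meet the stated rule.

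**The case against.** The strongest reply is that 9.1 states an aim and 9.4.3 is the analysis section, with formulas and named acceptance criteria. Apart from the AAFE = 2 boundary, 9.4.3 is the stricter of the two, and nothing says that meeting 9.1 alone is enough. The swapped label does little harm when 9.4.3 defines both metrics by formula. This lowers the severity, but it does not say which section governs or whether AUC, concentrations or both must pass.

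A second reply is that this is a small pilot, that 8.1 and 9.4.3 treat the PBPK work as secondary, and that a strict gate is defensible for a model that informs paediatric dosing. That is a fair argument for keeping a demanding check. It does not justify a pass/fail threshold placed at the expected value of a correct model.

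Three stronger readings are tempting, and the protocol does not support them:

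- A reader might infer that 9.1 accepts a model that halves every concentration. Exact halving gives AAFE 2.00, which fails the strict limit. Only near-halving, such as 0.51, passes.
- A reader might infer that a correct model is rejected at almost even odds. That needs each child's two values to fall in or out together without exception: 1 − 0.9^6 = 47% with 6 children. The same assumption with 11 children (10 of 11 needed) gives 30%, below the independent figure. The supportable range with complete sampling is 34–39%.
- A reader might infer that a model failing coverage is discarded. The protocol does not say what follows a failed criterion.

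**Conclusion.** Both parts hold. The acceptance rules in 9.1 and 9.4.3 are incompatible, and a model whose constant predicted/observed ratio lies in 0.50–0.70 or 1.30–2.00 (ends excluded) would be verified by one and fail the other. This assumes that the same ratios are put through both sections, which 9.1 does not strictly provide for because it is written for AUC.

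The coverage rule rejects a correct model about 34%, 38% or 35% of the time with 12, 22 or 30 values. These figures assume that only TXA recipients are informative, that every child gives both samples, and that 90% means at least 90%. Within-child correlation up to 0.95 hardly changes them; incomplete sampling can change them a good deal.

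This is a should-fix: it concerns a stated decision threshold, and the remedy is wording.

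**What to change.** Use one set of metrics, labels and limits in both sections: the two-sided 9.4.3 set, with AFE 0.7 to 1.3 for bias and AAFE at most 2 for precision, computed in TXA recipients. State explicitly whether it applies to concentrations, AUC or both, so that the AUC criterion in 9.1 is not dropped without comment.

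For coverage, report the observed proportion with its exact confidence interval and do not reject on the point estimate alone. For example, count coverage as failed only when a one-sided exact binomial test against 90%, at the number of samples actually obtained, shows it to be lower. At the 5% level a model then passes with at least 9 of 12 or at least 17 of 22 inside (P(X ≤ 8) = 0.026 and P(X ≤ 16) = 0.018 under 90% coverage), and a correct model passes 97% and 98% of the time. The test, not these counts, should be written into the protocol, because the number of samples may differ.

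The cost is a few sentences in 9.1 and 9.4.3, and a more permissive coverage check. At 75% true coverage a model would pass 65% of the time with 12 values (16% now) and 52% with 22 (6% now). At 60% true coverage the figures are 23% against 2%, and 7% against 0.2%. With so few samples, coverage cannot be the main safeguard, and the AFE and AAFE limits must carry the main check.
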